# A novel hand-assisted laparoscopic versus conventional laparoscopic right hemicolectomy for right colon cancer: study protocol for a randomized controlled trial

**DOI:** 10.1186/s13063-017-2084-3

**Published:** 2017-07-26

**Keywords:** Hand-assisted laparoscopic surgery, Complete mesocolic excision, D3 lymphadenectomy, No-touch isolation technique, Polymerase chain reaction, Non-inferiority, Randomized controlled trial

## Abstract

**Background:**

Although conventional laparoscopic and hand-assisted laparoscopic surgery for colorectal cancer is widely used today, there remain many technical challenges especially for right colon cancer in obese patients. Herein, we develop a novel hand-assisted laparoscopic surgery (HALS) with complete mesocolic excision (CME), D3 lymphadenectomy, and a total “no-touch” isolation technique (HALS-CME) in right hemicolectomy to overcome these issues. According to previous clinic practice, this novel procedure is not only feasible and safe but has several technical merits. However, the feasibility, short-term minimally invasive virtues, long-term oncological superiority, and potential total “no-touch” isolation technique benefits of HALS-CME should be confirmed by a prospective randomized controlled trial.

**Methods/design:**

This is a single-center, open-label, noninferiority, randomized controlled trial. Eligible participants will be randomly assigned to the HALS-CME group or to the laparoscopic surgery with CME, D3 lymphadenectomy, and total “no-touch” isolation technique (LAP-CME) group, or to conventional laparoscopic surgery with CME and D3 lymphadenectomy (cLAP) group at a 1:1:1 ratio using a centralized randomization list. Primary endpoints include safety, efficacy, and being oncologically clear, and 3-year disease-free, progression-free, and overall survival. Second endpoints include operative outcomes (operation time, blood loss, and incision length), pathologic evaluation (grading the plane of surgery, length of proximal and distal resection margins, distance between the tumor and the central arterial high tie, distance between the nearest bowel wall and the same high tie, area of mesentery resected, width of the chain of lymph-adipose tissue, length of the central lymph-adipose chain, number of harvested lymph nodes), and postoperative outcomes (pain intensity, postoperative inflammatory and immune responses, postoperative recovery).

**Discussion:**

This trial will provide valuable clinical evidence for the feasibility, safety, and potential total “no-touch” isolation technique benefits of HALS-CME for right hemicolectomy. The hypothesis is that HALS-CME is feasible for the radical D3 resection of right colon cancer and offers short-term safety and long-term oncological superiority compared with conventional laparoscopic surgery.

**Trial registration:**

ClinicalTrials.gov, NCT02625272. Registered on 8 December 2015.

**Electronic supplementary material:**

The online version of this article (doi:10.1186/s13063-017-2084-3) contains supplementary material, which is available to authorized users.

## Background

### Rationale

Since the first laparoscopic colon resection was performed in the 1990s, laparoscopic surgery had gained popularity for colon cancer, having fewer complications, a shorter length of hospital stay, and a quicker return to daily living and work when compared with traditional surgery [1, 2]. Furthermore, several randomized trials have demonstrated more favorable long-term cancer-specific or overall survival in laparoscopic colon surgery [3–5]. In recent years, progress in the treatment of colon cancer mainly includes that: 1) both European complete mesocolic excision (CME) with central vascular ligation (CVL) and Japanese D3 lymphadenectomy were demonstrated to have oncological superiority compared with traditional surgery [6–8]; 2) the feasibility and safety of laparoscopic right hemicolectomy with CME or D3 lymphadenectomy for right colon cancer has been confirmed [9–11].

Although it has a number of advantages, some drawbacks such as loss of tactile feedback, impaired hand-eye coordination, long operation time, and long learning curve still exist in laparoscopic surgery [12]. Moreover, these difficulties will become more obvious in laparoscopic right hemicolectomy for the high vascular variation in the right colon. In order to solve these problems, hand-assisted laparoscopic surgery (HALS) has been developed. Although HALS returns the sense of touch to the surgeon and the hand-assisted devices lower the threshold for surgeons to attempt laparoscopic techniques, people argue that HALS associated with rough visceral manipulation and the inadequate “no-touch” technique results in tumor cell spread [12, 13]. In addition, as far as we know, HALS with CME in right hemicolectomy is rarely reported in the literature.

Based on the above considerations, we developed a novel HALS with CME, D3 lymphadenectomy, and total “no-touch” isolation technique (HALS-CME) in right hemicolectomy to overcome these issues. According to our previous experience, this novel approach is not only feasible and safe but promises several technical merits.

### Objective and hypothesis

The objective of this trial is to evaluate the feasibility, short-term safety, long-term oncological superiority, and potential benefits of the “no-touch” isolation technique. The hypothesis is that the novel HALS-CME techniques is more consistent with the “no-touch” isolation technique, and is feasible for radical D3 lymphadenectomy, and could offer short-term safety, fast convalescence, and long-term oncological superiority.

## Methods and design

### Study design and setting

This is a single-center, open-label, noninferiority, randomized controlled trial undertaken at West China Hospital of Sichuan University (Chengdu, Sichuan, China), which performs 2000 colorectal cancer resections per year. The chief surgeon performs more than 400 laparoscopic-colorectal cancer resections per year. Participants will be randomly assigned to three parallel groups at a 1:1:1 ratio using a centralized randomization list. Patients assigned to the HALS-CME group will receive the hand-assisted laparoscopic surgery with CME, D3 lymphadenectomy, and total “no-touch” isolation technique (HALS-CME). Patients in the LAP-CME group will receive laparoscopic surgery with CME, D3 lymphadenectomy, and total “no-touch” isolation technique. Meanwhile, patients in cLAP group will receive conventional laparoscopic surgery with CME and D3 lymphadenectomy (Fig. 1). Blood samples and peritoneal washes will be collected from each participant during the operative procedure. Recruitment began on December 2015, and the trial is expected to proceed for 3 years.

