## Sample size and statistical analysis

As the primary aim of the prospective trial is exploratory, no sample size calculation is performed. The statistical tests will be performed in the SPSS software program (version 13.0, SPSS, Chicago, IL, USA). A two-sided *P* value less than 0.05 will be considered statistically significant. Descriptive statistics will be used for baseline demographic and clinical characteristics of participants (i.e., mean and standard deviation for continuous variables, proportions for categorical variables). A χ^2^ test or Fisher’s exact test will be applied for categorical variables. Student’s *t* test or the Mann-Whitney *U* test will be used for continuous variables. Kaplan-Meier curves and log-rank analysis will be used to compare the differences in DFS and OS among the three parallel groups.

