There are potential limitations in this trial. 1) The trial will be carried out in only one center, which may impact participant recruitment and limit the applicability of the outcomes to other centers. 2) The open-label nature of the trial may cause biased estimates of the treatment effect. However, it is not possible to blind the surgeon for the special nature of nonpharmacologic trials. Although the surgeons, researchers, and participants are not blinded, the pathologists, statisticians, and follow-up staff will be blinded to the group assignment, which contributes to reducing the treatment effect estimation bias. 3) The relatively short follow-up time has an impact on comparing long-term outcomes. In summary, if the feasibility, short-term safety, long-term oncological safety, and potential total “no-touch” isolation technique benefits of HALS-CME are verified, this technique could be recommended as a new approach to overcome the technical challenges in right hemicolectomy for right colon cancer.

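### The trial is labelled noninferiority, but its objective is superiority, its stated aim is exploratory and its tests look only for difference, so the design as described cannot support a noninferiority conclusion

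*Protocol article*

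**What the plan says.** All references are to the protocol article.

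- **Noninferiority.** The abstract (Methods/design) states: "This is a single-center, open-label, noninferiority, randomized controlled trial". Study design and setting repeats it: "This is a single-center, open-label, noninferiority, randomized controlled trial undertaken". The keyword list also includes the term.
- **Superiority.** Objective and hypothesis: "The objective of this trial is to evaluate the feasibility, short-term safety, long-term oncological superiority". The hypothesis in the same section is that the new technique "could offer short-term safety, fast convalescence, and long-term oncological superiority". The abstract's Discussion paragraph adds a comparator: the technique "offers short-term safety and long-term oncological superiority compared with conventional laparoscopic surgery". The abstract's Background says that such superiority is to be confirmed by a randomized trial.
- **Exploratory.** Sample size and statistical analysis: "As the primary aim of the prospective trial is exploratory, no sample size calculation is performed".
- **Analysis.** In the same section, a two-sided P "value less than 0.05 will be considered statistically significant". The methods listed are chi-square or Fisher's exact, t or Mann-Whitney, and Kaplan-Meier with log-rank across the three groups.
- **Conclusion foreseen.** The end of the Discussion says that, if feasibility, short-term safety, long-term oncological safety and the no-touch benefits are verified, "this technique could be recommended as a new approach to overcome the technical challenges".

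**The concern.** Noninferiority, superiority and exploration ask different things of the same data. A noninferiority claim needs a named endpoint, a named reference arm, a margin, and a rule that compares a confidence interval with that margin. A superiority claim needs a rejected null of no difference. An exploratory study estimates and makes neither claim. The article asserts all three framings and does not say which applies to which endpoint or contrast.

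The listed tests all have a null of no difference. A small P value from them can support a difference. A large P value supports nothing, because it arises from equivalence and from too little information alike. With a noninferiority label and only difference tests, the one listed result that resembles noninferiority is P>0.05. What is at stake is that a survival deficit of clinical importance could pass unnoticed under a label that suggests it was ruled out.

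**Working it through.** **Step 1. Compare the statements.** The article states no sample size, margin, event rate or power, so there is no figure to reproduce. The check is first one of consistency.

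| Element a noninferiority trial needs | What the article states |
|---|---|
| Hypothesis of not being worse by more than a margin | Long-term oncological superiority |
| Endpoint carrying the claim | Primary outcomes include safety, efficacy, oncological clearance, tumour-cell shedding by RT-PCR, 3-year DFS, PFS, OS and recurrence pattern; none is assigned to noninferiority |
| Reference arm | Two control arms (LAP-CME and cLAP); neither is named as the noninferiority reference |
| Analysis against a margin | Two-sided tests of no difference at 0.05 |
| Size or precision chosen for the claim | None calculated, because the aim is exploratory |

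No row matches the label.

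**Step 2. How uninformative P>0.05 can be (illustration).** Every input except the 0.05 level is an assumption: true 3-year DFS of 80% in the control arm and 70% with the new technique, arm sizes n, and one pairwise log-rank test. The article specifies a log-rank across three groups, so this is a simplification.

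- Hazard ratio = ln(0.70)/ln(0.80) = 0.3567/0.2231 = 1.60, so ln HR = 0.469.
- Expected events = n × (0.20 + 0.30) = 0.5n.
- P(non-significant) = 1 − Φ(0.469 × √(events/4) − 1.96).
- n = 50: 25 events; 0.469 × 2.50 = 1.17; 1 − Φ(−0.79) = 0.78.
- n = 100: 50 events; 0.469 × 3.54 = 1.66; 1 − Φ(−0.30) = 0.62.
- The same formula gives 0.85 at n = 30 and 0.47 at n = 150.

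A two-proportion test on the same rates gives nearly the same values: 0.86, 0.79, 0.63 and 0.48 at 30, 50, 100 and 150 per arm.

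**Step 3. What a margin would demand (illustration).** Assume both arms are truly at 80% and the margin is 10 points.

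- 95% CI half-width = 1.96 × √(2 × 0.8 × 0.2/n): 0.157 at n = 50 and 0.111 at n = 100.
- Chance of meeting the margin = Φ(0.10/√(0.32/n) − 1.96): Φ(1.25 − 1.96) = 0.24 at n = 50; Φ(1.77 − 1.96) = 0.42 at n = 100.
- Patients per arm for 80% power at one-sided 0.025 = 0.32 × (1.96 + 0.84)²/0.10², about 252. Over control rates of 70% to 85% the range is 330 down to 201. For a 5-point margin it is 1319 down to 801, and for a 15-point margin 147 down to 89.

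The spread shows that whether a noninferiority claim is within reach depends on the margin and the size, and the article gives neither.

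**The case against.** Several objections have force.

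- **The margin may be in a document not shown.** This is correct as far as it goes. The absence of a margin or an interval rule from a journal article proves little, and a reader should not infer that no margin exists anywhere. The point rests instead on statements the article does make. It does not defer the sample size; it says none was calculated and gives an exploratory aim as the reason. An unseen plan would not remove that conflict with the label.
- **A trial may seek noninferiority on one endpoint and superiority on another.** That is a legitimate design, and the superiority wording attaches only to long-term oncological outcome. But the article nowhere makes that assignment, and its Discussion moves from oncological superiority to oncological safety.
- **Nothing says a non-significant result will be called noninferior.** True. A reader might infer that it would be, but the article says only when a result is significant. The supportable statement is that it could be misread so.
- **The Discussion is not a plan to recommend.** Also true. The sentence is conditional and follows a list of limitations, including short follow-up.
- **The illustrative figures depend on the chosen sizes.** They do. The article gives no total, so the trial cannot be called small. Under the same assumptions, 286 per arm (143 events) gives Φ(0.469 × 5.98 − 1.96) = 0.80 power for the difference and Φ(0.10/√(0.32/286) − 1.96) = 0.85 for the 10-point margin.
- **The exploratory statement already warns the reader.** Partly. It appears once, in the statistical section, while the noninferiority label is in the abstract, keywords and design section.

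**Conclusion.** The concern holds as an inconsistency in the stated text. The article calls the trial noninferiority in three places, states superiority as objective and hypothesis, and describes an exploratory study analysed by tests of difference. With no endpoint or reference arm tied to noninferiority, the design and analysis as described cannot support that conclusion.

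This verdict needs none of the illustrative numbers. They show only how weak P>0.05 can be as evidence. With a true 10-point DFS deficit, a pairwise test would miss it about 78% of the time at 50 per arm and 62% at 100 per arm. Those figures rest on assumed rates, assumed arm sizes and a two-arm comparison, and they fall as the arms grow. The documents do not support the stronger claim that the trial will report false noninferiority.

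**What to change.** **Preferred change.**

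1. Delete noninferiority from the keywords, the abstract and Study design and setting.
2. Recast the superiority wording in the abstract's Background and Discussion and in Objective and hypothesis as exploratory, in line with the statistical section.
3. Report each prespecified pairwise contrast (HALS-CME versus LAP-CME, HALS-CME versus cLAP) as a difference or hazard ratio with its 95% confidence interval.
4. State that P>0.05 will not be read as noninferiority or as safety.
5. Align the conditional closing sentence of the Discussion with what an exploratory comparison can show.

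The cost is wording and a weaker claim. No extra patients are needed.

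**If the label is kept.** The sponsor must name one endpoint, one reference arm and a justified margin before comparative outcome data by arm are examined, judge the claim only by whether the confidence interval excludes the margin, and state the precision or sample size this requires. This route may need more patients. It is also harder to defend for perioperative endpoints, because the trial is open-label and has recruited since December 2015, so those results may already be known to unblinded staff.

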**Fig. 1 Fig1:**
[figure not shown]
Participants flow through the trial. *cLAP* conventional laparoscopic surgery with CME and D3 lymphadenectomy, *CME* complete mesocolic excision, *HALS-CME* hand-assisted laparoscopic surgery with CME, D3 lymphadenectomy, and total “no-touch” isolation, *LAP-CME* laparoscopic surgery with CME, D3 lymphadenectomy, and total “no-touch” isolation

### Ethical considerations and registration

This trial protocol has been approved by the Biological and Medical Ethics Committee of West China Hospital (2015 trial number (130)) and has been registered at the Clinical Trial Registry as NCT02625272 on 8 December 2015. All of the eligible participants will be informed of the potential risks and benefits of intervention in each group. A signed written informed consent will be obtained from each patient. All the results will be presented with the CONSORT (Consolidated Standards of Reporting Trials) statement (Additional file 1).

## Participants

Patients aged 18 to 80 years diagnosed with right colon cancer via abdominal enhanced computed tomography (CT) and total colonoscopy will be further screened for inclusion and exclusion.

### Inclusion criteria

Prior to enrollment in the study, patients must fulfill all of the following criteria:Diagnosed with right colon cancer: ileocecum cancer, ascending colon cancer, hepatic flexure colon cancerAccording to the 7th Edition of the American Joint Committee on Cancer (AJCC) Cancer Staging Manual, preoperative clinic stages: cT1-4a, N0-2a, M0No preoperative radiochemotherapy for cancerNo past significant operative historyEastern Cooperative Oncology Group (ECOG) performance status: 0 to 2American Society of Anesthesiologists (ASA) classification: 1 to 3

### Exclusion criteria

Patients will be excluded for any of the following reasons:Other sites of cancer such as transverse colon, descending colon, sigmoid colon, and rectumDistant metastases evident on chest, abdominal, and pelvic CT scanEmergency condition caused by cancer: bleeding, perforation, obstructionPrevious significant abdominal surgery (except appendectomy, cholecystotomy)Severe mental diseaseMalignant disease within the previous 5 years

## Outcome measures

### Primary outcomes

The primary endpoints are safety, efficacy, and being oncologically clear. Perioperative morbidity will be divided into intraoperative morbidity observed during the operation and postoperative morbidity observed during the hospital stay and within 30 days at the outpatient clinic. Postoperative morbidity will be assessed according to the Clavien-Dindo classification. Real-time polymerase chain reaction (RT-PCR) will be used to test whether the novel total “no-touch” isolation technique could potentially reduce tumor cells shedding into the portal circulation, peripheral circulation and peritoneal cavity. Other primary outcomes include 3-year disease-free survival (DFS), progression-free survival (PFS), overall survival (OS), and recurrence pattern (local recurrence, metastasis).

### Secondary outcomes

Secondary endpoints will be measured and recorded prospectively on a case report form (CRF). Intraoperative outcomes include operation time, blood loss, intraoperative complications, and incision length. Pathologic evaluation includes tumor size, grading the plane of surgery (mesocolic plane, intramesocolic plane, muscularis propria plane), length of proximal and distal resection margins, distance between the tumor and the central arterial high tie, distance between the nearest bowel wall and the same high tie, area of mesentery resected, width of the chain of lymph-adipose tissue (the width of the central lymph node region through the high tie), length of the central lymph-adipose chain (the length of the central lymph node region through the high tie), and number of harvested lymph nodes. Postoperative inflammation and immune response (procalcitonin (PCT), C-reactive protein (CRP), interleukin (IL)-6) will be measured at 24 h, 72 h, and 120 h postoperatively. A horizontal visual analogue scale with a 0 to 10 cm scale will be used to measure pain intensity on postoperative days 1, 3, and 5. Postoperative recovery including time to first flatus, liquid diet, and duration of hospital stay will be recorded daily in hospital.

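### Pain and the three inflammatory markers are measured on three postoperative days, but only two-sample tests at P<0.05 are named; one repeated-measures analysis per measure would be better

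*Protocol article*

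**What the plan says.** Under Objective and hypothesis, the protocol article expects that HALS-CME "could offer short-term safety, fast convalescence, and long-term oncological superiority". No outcome or time point is attached to the convalescence part.

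The postoperative measures that could bear on it are under Secondary outcomes:

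- Inflammation and immune response: "procalcitonin (PCT), C-reactive protein (CRP), interleukin (IL)-6", which "will be measured at 24 h, 72 h, and 120 h postoperatively. A horizontal visual analogue scale with a 0 to 10 cm scale" (the last words of this quote open the sentence on pain).
- Pain: that visual analogue scale "will be used to measure pain intensity on postoperative days 1, 3, and 5".
- Recovery: time to first flatus, time to liquid diet, and length of hospital stay.

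Table 1 repeats these times, ranks nothing, and adds a preoperative value for the inflammatory markers (not for VAS).

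Under Sample size and statistical analysis, one rule covers everything: "A two-sided *P* value less than 0.05 will be considered statistically significant". For continuous data, Student's t "test or the Mann-Whitney *U* test will be used for continuous variables". No repeated-measures method is named. The same section calls the primary aim exploratory, as the reason for not calculating a sample size.

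**The concern.** A two-sample test takes one value per patient. Applied to a measure recorded at three times, the stated method most naturally becomes three tests, one per day. Four such measures give 12 tests per arm pair, and the recovery times add three. Each would be judged at 0.05, and nothing says how the results combine into an answer on convalescence.

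Two things are at stake. First, an isolated result, such as a lower CRP at 72 h with no difference in hospital stay, could be presented as support for the hypothesis, because nothing in the plan marks it as description. Second, testing each day separately discards the information in a patient's other two values. Both arise within a single comparison such as HALS-CME versus cLAP, so they are separate from the number of arms and of primary endpoints.

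**Working it through.** The protocol gives no familywise error rate, power or sample size, so there is no figure of its own to reproduce. The check is a count, an error calculation and an information calculation.

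**1. Count per arm pair** (Secondary outcomes)

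- Markers: 3 × 3 times = 9
- VAS: 3 days = 3
- Recovery times: 3
- Total: 9 + 3 + 3 = 15, of which 9 + 3 = 12 are time points of four measures.

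**2. Chance of at least one P<0.05 with no true difference, one arm pair**

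With k independent tests, the chance in either direction is 1 − 0.95^k, and the chance of a result favouring HALS-CME is 1 − 0.975^k. For k = 15:

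- Either direction: 1 − 0.95^15 = 53.7%
- Favouring HALS-CME: 1 − 0.975^15 = 31.6%

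The outcomes will be correlated. The protocol gives no correlations, so a common correlation ρ among the test statistics is an assumption, varied from 0 to 0.8. With a shared normal component u and c = 1.96, the either-direction chance is 1 − E{[Φ((c − √ρ·u)/√(1−ρ)) − Φ((−c − √ρ·u)/√(1−ρ))]^k}. The one-direction chance drops the second Φ term.

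| Tests | Direction | ρ = 0 | ρ = 0.5 | ρ = 0.8 |
|---|---|---|---|---|
| All 15 | either | 53.7% | 36.1% | 20.2% |
| All 15 | favouring HALS-CME | 31.6% | 18.1% | 10.1% |
| 3 recovery times | either | 14.3% | 12.5% | 9.8% |

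As a sensitivity check, a block structure (higher correlation within a measure than between measures) was simulated with 200,000 replicates. From independence to correlations of 0.8 within and 0.5 between measures, it gave 54% down to 32% in either direction and 32% down to 16% favouring HALS-CME. The either-direction range of 20% to 54% covers both structures.

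**3. One analysis per repeated measure**

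Twelve comparisons become four. With the three recovery times, 4 + 3 = 7 per pair. If independent, the chances are 1 − 0.95^7 = 30.2% in either direction and 1 − 0.975^7 = 16.2% favouring HALS-CME. The error falls but does not reach 5%, so the remaining results still need a descriptive label.

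**4. Information gained**

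Suppose the effect is constant over the three times, the variances are equal, and the within-patient correlation is r. The mean of three values has variance (1 + 2r)/3 relative to a single day, so the information ratio is 3/(1 + 2r):

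- r = 0.8: 3/2.6 = 1.15
- r = 0.5: 3/2 = 1.5

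**The case against.** The strongest reply is that the family of 15 is imposed from outside. The protocol treats inflammation, pain and recovery as separate domains, in the Secondary outcomes text and as separate rows of Table 1. Convalescence maps most naturally onto the three recovery times, where the figure is 10% to 14%. This stands: the 15-test figure describes all the postoperative candidates together, not a family that the protocol defines. The Abstract's statement that the technique's benefits "should be confirmed by a prospective randomized controlled trial" adds little. It mentions short-term minimally invasive virtues, but the Table 1 footnote defines the minimally invasive evaluation by four operative measures, none of them among the 15.

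Second, separate testing of each day is an inference. The section lists tests by type of variable and never says that every time point is tested. A repeated-measures analysis, or a hierarchy of secondary outcomes, could sit in a fuller document that is not shown. This also stands, and it is why the absence of a single deciding outcome is not counted here as an error. What the article does state for continuous data, however, is a two-sample test, and for these four measures a better method exists.

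Third, unadjusted secondary testing is ordinary in an exploratory trial and does harm only if a claim is drawn from it. That is right in principle. But the word exploratory describes the primary aim and explains the missing sample size; the significance rule that follows applies without exception, and the convalescence hypothesis can draw only on secondary outcomes.

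A reader might also infer that a spurious advantage for HALS-CME is likely. The figures do not support that: about 10% to 32% for one pair is appreciable but below even odds. Nor do these percentages contradict a stated 5%, because the protocol's 0.05 is a per-test threshold.

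**Conclusion.** The point holds as a minor, inexpensive improvement. A convalescence hypothesis is stated, and the only method given for four repeatedly measured outcomes is a two-sample test with every P<0.05 called significant. Read that way, one arm pair carries 15 unadjusted comparisons, with a chance of about 20% to 54% of at least one significant difference in either direction and about 10% to 32% of one favouring HALS-CME. If only the recovery times count, the either-direction figure is 10% to 14%.

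These figures assume no true difference, one arm pair, day-by-day testing, and correlations that the protocol does not give. They do not touch the primary endpoints, and they do not show that the trial plans to claim confirmation from a single-day result.

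**What to change.** In Sample size and statistical analysis:

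1. State that VAS and each of PCT, CRP and IL-6 will be analysed in one repeated-measures model over the three postoperative time points, giving one overall arm effect per measure. The preoperative marker values in Table 1 can enter as a baseline covariate.
2. Present day-specific differences as description only.
3. State that the secondary postoperative results are reported as estimates with 95% confidence intervals and do not by themselves confirm the convalescence hypothesis.

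Whether to name one deciding recovery outcome is for the investigators. Any such choice should allow for the fact that surgeons and participants are not blinded.

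The cost is a few sentences and somewhat different analysis code, with no extra patients or measurements. There are two downsides: an isolated single-day P<0.05 can no longer be claimed, and an effect confined to one day is diluted in the overall estimate.
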